#### Exclusion criteria

The study excludes participants who have infertility due to congenital reproductive system physiological defects or malformations; hereditary factors; oviduct defects; immune factors; uterine fibroids; adenomyosis or endometriosis; spouses with reproductive defects; severe abnormalities of the cardiovascular system, liver function, kidney function or hemopoietic system; or allergies to experimental drugs.

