### Withdrawal criteria

Participant have the right to withdraw from the study, as defined in the informed consent document, or to “drop out” if they do not explicitly withdraw from the study but are no longer undergoing training and testing. The reason for withdrawal should be understood as far as possible and recorded, for example, perceiving lack of efficacy; intolerance of certain adverse effects; inability to continue the clinical study; and lost to follow-up without explanation. Case record forms for withdrawn participant will be kept, and the results of the last trial will be considered final.

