#### Abnormal uterine bleeding-ovulatory disorders (AUB-O)

Uterine bleeding has no cyclicity or regularity, and the bleeding amount cannot be estimated. Anemia or hemorrhagic shock will mark severe cases.Excludes bleeding caused by pregnancy or pregnancy-related factors, bleeding after menopause, bleeding from the genital tract except the uterus or from nongenital organs, iatrogenic bleeding, and bleeding caused by systemic disease.Basal body temperature (BBT) appears as a single phase.One or more sex hormone levels are beyond the normal range, including follicle-stimulation hormone (FSH), luteinizing hormone (LH), prolactin (PRL), estradiol (E_2_), progesterone (P), and testosterone (T).

AUB-O will be diagnosed if both (1) and (2) are met and at least one of (3) and (4) is met [16].

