### Safety analysis

Safety will be analyzed by adverse events (AEs); laboratory tests, including routine blood and urine tests, liver and renal function tests; and ECG. AEs will be recorded at every visit, and the other tests will be done at the baseline visit and end-of-treatment visit. Every AE will be recorded in detail, including the starting time and ending time, severity, characteristics (continuous or paroxysmal, and the frequency), any relationship with the drugs used in the study, the outcome, use or nonuse of corrective treatment, and whether the woman drops out of the study because of the AE. In this study, common AEs will include nausea, loose stool with dark color, and mild pain in the lateral lower abdomen on ovulation day, which are not expected to be severe and have no need of intervention. If the participant has serious adverse events (SAEs) leading to extended hospitalization, death, or a status that the PI considers unsuitable for further study, she will be removed from the trial as soon as possible and provided proper treatment. Every SAE will be recorded in the CRF and reported to the ethics committee and related health administrative department.

The degrees of safety analysis are divided into 4 grades according to the AE and the safety index profile:
Grade 1: The participant is safe without any AE. There is no abnormal result in the safety index.Grade 2: The participant is relatively safe with a mild AE. The adverse reaction has no need of treatment, and the participant can continue the study. There is no abnormal result in the safety index.Grade 3: There is moderate AE, or there is a mildly abnormal result in safety index. The participant can continue the study after corrective intervention for the AE.Grade 4: The participant should be removed due to the SAE, or there is a moderate or serious abnormal result in safety index.

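### The four-grade safety scale ignores each woman's baseline test results and leaves some adverse events without a grade

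*Protocol article*

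**What the plan says.** The Safety analysis section of the protocol article defines four grades from AEs and the safety index:

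- "Grade 1: The participant is safe without any AE. There is no abnormal result in the safety index".
- "Grade 2: The participant is relatively safe with a mild AE"; this grade also requires that the reaction needs no treatment, that she can go on in the study, and that no test is abnormal.
- "Grade 3: There is moderate AE, or there is a mildly abnormal result in safety index". The next sentence adds: "The participant can continue the study after corrective intervention for the AE".
- "Grade 4: The participant should be removed due to the SAE, or there is a moderate or serious abnormal result in safety index".

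The same section says that laboratory tests and ECG are done at baseline and at the end of treatment. It also says that severity, and any dropout because of the AE, are recorded for every AE. Its description of a serious AE (SAE) includes a state that the PI judges unsuitable for further study.

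Three other sections bear on the point. Exclusion criteria bars "severe abnormalities of the cardiovascular system, liver function, kidney function or hemopoietic system", so milder abnormalities may enter. The diagnostic criteria for AUB-O, one of the six enrolled diseases, say "Anemia or hemorrhagic shock will mark severe cases". Withdrawal criteria lists "intolerance of certain adverse effects" among the reasons a participant may leave.

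**The concern.** A safety grade should reflect what happened after treatment began. This one depends on whether a result is abnormal, not on whether it became abnormal or got worse. Findings that were present at entry therefore enter the upper grades in both arms and make a real difference harder to see.

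On the AE side the steps are mild, moderate and then SAE. Severity and seriousness are different scales, and a severe event that is not serious falls between the steps. Grades 2 and 3 also speak of a participant who can continue, so a woman who leaves because she cannot tolerate an AE may fit neither. If the combined grade is tabulated by arm, some informative participants would have no row.

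**Working it through.** The article states no figure for this point, so there is nothing to reproduce. The check has three parts.

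**1. Baseline.** Take a woman with AUB-O who enters with a non-severe low haemoglobin, has no AE, and ends treatment with a higher but still low value.

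- Grade 1 fails, because a result is abnormal.
- Grade 2 fails, because it needs a mild AE and no abnormal result.
- Grade 3 applies if the final value is mildly abnormal, and Grade 4 if it is moderately abnormal.

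She improved, and is classed as a safety problem.

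**2. Exhaustiveness.** Cross AE type (none, mild, moderate, severe non-serious, SAE) with treatment needed (yes/no), can continue (yes/no) and worst test (normal, mildly abnormal, moderately or seriously abnormal). With no AE, only untreated and continuing is possible (3 profiles). An SAE is taken as not continuing (6). The other three AE types have 12 each. The total is 3 + 3 × 12 + 6 = 45.

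If the continuation wording in Grades 2 and 3 is a condition, 15 of the 45 profiles get no grade:

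| Profile | Ungraded |
|---|---|
| Severe non-serious AE, normal tests | 4 |
| Severe non-serious AE, mildly abnormal test, cannot continue | 2 |
| Mild or moderate AE, cannot continue, tests normal or mildly abnormal | 8 |
| Mild AE that needs treatment, continues, normal tests | 1 |

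Two more lenient readings narrow this:

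- If the Grade 3 continuation sentence is only descriptive, every moderate AE and every mildly abnormal test is graded. The 4 moderate profiles drop out, as do the 2 mild and 2 severe profiles with a mildly abnormal test, which leaves 15 − 8 = 7. All 4 severe non-serious profiles with normal tests are among them.
- If every removal decided by the PI counts as an SAE, and so as Grade 4, three kinds of gap remain: the severe non-serious AE in a woman who continues with normal tests, the woman who withdraws herself because of an AE, and the treated mild AE.

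**3. Size of the background.** The notes to Table 1 list nine blood values (RBC, Hb, WBC, PLT, ALT, AST, BIL, BUN, Cr) and three urine items; ECG makes 13. Let q be the chance that one item is called abnormal with no drug effect. The article does not give q, so it is an assumption. With independent items, P(at least one abnormal) = 1 − (1 − q)^n:

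| q | n = 9 (blood) | n = 13 (blood, urine, ECG) |
|---|---|---|
| 0.5% | 4% | 6% |
| 1% | 9% | 12% |
| 2.5% | 20% | 28% |
| 5% | 37% | 49% |

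To illustrate dilution, assume true new abnormalities of 5% and 15% in the two arms and a background share b in both. The observed proportions are b + (1 − b) × 0.05 and b + (1 − b) × 0.15, so the difference shrinks to (1 − b) × 10 points. Power is for a two-sided 0.05 comparison of two proportions with 219 per arm, the article's number before the dropout allowance:

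| b | Observed proportions | Difference | Power |
|---|---|---|---|
| 0 | 5.0% v 15.0% | 10.0 points | 94% |
| 12% | 16.4% v 25.2% | 8.8 points | 62% |
| 28% | 31.6% v 38.8% | 7.2 points | 35% |
| 49% | 51.6% v 56.7% | 5.1 points | 19% |

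**The case against.** The strongest reply is that the grade is an extra composite. The section opens by saying that safety is analysed by AEs, laboratory tests and ECG, and severity and AE-related dropout are recorded for each event. The grade is neither a primary nor a secondary outcome, and Statistical analysis attaches no test or decision to it. All of this stands. A reader might infer that the scale is the trial's only safety summary, or that women who leave because of AEs are lost from the safety data. The article supports neither.

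A reader might also infer that no AE withdrawal has a grade. That is too broad, because a removal decided by the PI can reach Grade 4 through the SAE wording. The gap is self-withdrawal, and even there a lenient reading of Grade 3 would take in the moderate AEs.

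Nor does the text say that any value outside its reference range is abnormal. It leaves the word undefined, and the full protocol may define it. The higher percentages above depend on a wide meaning. A narrower cutoff would shrink the background but would still not introduce a comparison with baseline.

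Finally, a reader might conclude that the scale biases the comparison between arms. Randomization should balance pre-existing abnormalities, so dilution is what can be claimed. The AUB-O example is limited too: anaemia is tied to severe cases, severe haemopoietic abnormality is excluded, and AUB-O is one of six diseases whose share is not given.

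The reply that such detail belongs in an analysis plan does not fully answer the point. The four grades are written out in full, and a plan that followed them would misclassify.

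**Conclusion.** The point holds for the combined grade and no further. As written, the scale counts unchanged or improved pre-existing abnormalities as Grade 3 or 4 and so adds findings unrelated to the drug to both arms. It gives no grade to a severe non-serious AE with normal tests. On the plain reading, it also gives none to self-withdrawal because of a non-serious AE with normal tests.

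The size is uncertain. For the nine blood values the background runs from about 4% to 37% of unaffected women as q goes from 0.5% to 5%. This assumes independent tests; correlation between them would lower the figures somewhat, and non-severe anaemia at entry would add to them. The power figures rest on an assumed 5% versus 15% and show only that a modest background can matter.

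**What to change.** Reword the grade definitions for analysis:

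1. Count a blood, urine or ECG result only if it is newly abnormal, or worse than the woman's own baseline, and say what abnormal means. The baseline rule removes abnormalities that persist from entry; the definition limits those that arise by chance.
2. Assign severe non-serious AEs, AE-related self-withdrawals and treated mild AEs to a stated grade, so that every profile has one.
3. Derive an AE grade and a test grade separately and take the worse as the combined grade.

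This concerns classification in the analysis only and sets no rule on who stops treatment or leaves the trial.

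No new data are needed: baseline and end-of-treatment tests, AE severity and AE-related dropout are already collected. The cost is a protocol wording amendment, which under Ethics approval needs the committee's agreement, while Trial status reports recruitment as under way.

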### Data management and quality control of the data

All original data will be recorded in case report forms (CRFs). Two keyboard operators will type all data in the analysis system twice independently, and a verification of data consistency will be done. The data administrator will further examine the data by using a logical consistency check system to ensure the veracity of the data, and then the database will be locked for statistical analysis.

All clinical investigators and relevant staff will be trained in good clinical practice (GCP) and the study protocol before the study starts. After completing all training processes, they will receive authorization to perform the study.

#### Statistical analysis

An independent statistician will use SPSS 21.0 (SPSS, Chicago, Illinois, USA) to analyze the data.

The mean ± SD will be used to describe normally distributed data, while medians with IQRs will be used if the data are not normally distributed. The *χ*^2^ test will be used for evaluating differences between dichotomous variables, while one-way analysis of variance or Student’s *t* test will be used for evaluating continuous variables. The Mann-Whitney test will be used if the data are not normally distributed. A *p* value < 0.05 will be considered statistically significant.

If there are dropouts from the study, the last-observation-carried-forward principle will be used to compensate for the loss of data.

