**Methods:**

This is a randomized, double-blinded, double-dummy, parallel, positively controlled, adaptive, multicenter clinical trial. All participants will be randomly allocated by a central randomization system to the treatment group or the control group in a 1:1 ratio. The treatment group will undergo a 14-day treatment with Bushen Culuan Decoction 13 g three times a day and a 5-day treatment with clomiphene citrate placebo tablets 50 mg once a day starting on day 5 of every menstrual period. The control group will undergo a 14-day treatment with Bushen Culuan Decoction placebo 13 g three times a day and a 5-day treatment with clomiphene citrate tablets 50 mg once a day from day 5 in every menstrual period. The whole treatment will last through 3 menstrual periods or 6 menstrual periods, depending on whether ovulation is regained in the first 3 menstrual periods. All statistical analyses will be performed in SPSS 21.0 (SPSS, Chicago, Illinois, USA), and a *p* value < 0.05 will be considered statistically significant.

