### Objectives

The objective of this RCT is to evaluate whether Bushen Culuan Decoction enables a higher pregnancy rate than clomiphene citrate in women with anovulatory infertility and to identify the anovulatory diseases for which Bushen Culuan Decoction has higher effectiveness (among AUB-O, PCOS, hyperprolactinemia, LUFS, corpus luteum insufficiency, and POI).

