### Randomization

Using the stratified block randomization method, a special researcher at the Institute of Basic Research in Clinical Medicine, China Academy of Chinese Medical Sciences (IBRCM, CACMS) is responsible for compiling the number sequence table in turn, generating random numbers through SAS 9.3statistical software, determining them in the form of documents after coding, and keeping them by special personnel after sealing. According to the grouping results obtained, the clinical investigator gives the corresponding drugs to the patient according to the subject sequence number and drug number.

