### Baseline visit

Each participant who is eligible for the study as screened in the last step will be scheduled for a baseline visit. We will collect general vital signs, safety index, and effectiveness index before the treatment in this stage.

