### Outcome measures

#### Primary outcome

The primary outcome is pregnancy rate (confirmed by serum β-HCG positivity).

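### Pregnancy and the continuous outcomes are to be compared with unstratified, unadjusted tests despite stratified randomisation, six pooled diseases and recorded baselines: a loss of efficiency, not a false-positive risk

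*Protocol article*

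**What the plan says.** - **Randomisation.** The Randomization section begins "Using the stratified block randomization method" and names no stratification factor. The abstract's Methods allocate to "the treatment group or the control group in a 1:1 ratio".
- **Population and aims.** Objectives and Design compare arms across women with any of six diseases. A second aim is "to identify the anovulatory diseases for which Bushen Culuan Decoction has higher effectiveness".
- **Primary endpoint.** "The primary outcome is pregnancy rate", confirmed by serum β-HCG, so it is binary.
- **Tests.** Under Statistical analysis, the χ² "test will be used for evaluating differences between dichotomous variables, while one-way analysis of variance" or Student's t test is for continuous variables. For skewed data, "The Mann-Whitney test will be used if the data are not normally distributed". The threshold is that a p "value < 0.05 will be considered statistically significant". No stratified test, covariate, or centre or disease term appears.
- **Baseline data.** Baseline visit: "We will collect general vital signs, safety index, and effectiveness index before the treatment in this stage". The Effectiveness index list there covers sex hormones, AMH, inhibin B, coagulation, ultrasound measures and symptom score, which recur as secondary outcomes.

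**The concern.** Stratified randomisation balances the arms on the strata. If those strata predict outcome, the difference between arms varies less from trial to trial than an unstratified standard error supposes. A test that ignores the strata then rejects less often than its nominal level and has less power than the design paid for. Where a prognostic factor was not stratified, an unstratified test keeps its level but still forgoes the precision that the factor could supply.

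The same applies to the secondary outcomes. Most have a pre-treatment value on record, and the named tests make no stated use of it. A pooled χ² also says nothing on whether the effect differs between diseases, which is the second stated objective.

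At stake is power for pregnancy and precision for the secondary outcomes, both recoverable without another patient.

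**Working it through.** **1. The plan's own figure.** The article gives 219 per group from 90% against 80%, α 0.05 and β 0.10. With a mean rate of 0.85:

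n = (1.645 + 1.282)² × 2 × 0.85 × 0.15 / 0.10² ≈ 218.4, so 219.

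This is a one-sided calculation; the two-sided counterpart gives 268. A two-sided χ² with 219 per group has about 83.7% power at those rates. They are rates of total effectiveness, not pregnancy, and the sidedness is a separate matter. It is noted only because it leaves no power to spare.

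**2. How much variance the strata hold.** With equal numbers per disease and balanced arms within disease, the true variance of the pooled difference under the null, relative to what the χ² uses, is

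mean(pq) / (p̄q̄) = 1 − var(p) / (p̄q̄).

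The article gives no pregnancy rates by disease, so the control rates below are assumptions.

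| Control rates in the six diseases (%) | var(p) / (p̄q̄) | Variance ratio | SE too wide by | Implied level of a nominal 5% χ² |
|---|---|---|---|---|
| 30 in all | 0 | 1.000 | 0% | 5.0% |
| 20, 25, 30, 30, 35, 40 | 0.00417 / 0.21 | 0.980 | 1% | 4.8% |
| 10, 20, 25, 35, 40, 50 | 0.0175 / 0.21 | 0.917 | 4-5% | 4.1% |
| 5, 15, 25, 35, 45, 60 | 0.0337 / 0.2133 | 0.842 | 9% | 3.3% |

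The SE column is 1/√ratio − 1. The level is 2 × [1 − Φ(1.96/√ratio)]. In simulation the χ² level was 5.1%, 5.0%, 4.0% and 3.3%.

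**3. Power, χ² against Cochran-Mantel-Haenszel (CMH) by disease.** Two-sided 5%, randomisation stratified by disease.

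| Setting | Spread of control rates | χ² | CMH | Loss (points) |
|---|---|---|---|---|
| Odds ratio 2.0, 37 per arm per disease | equal, 30% | 94.3% | 94.2% | none |
| | 20-40% | 93.2% | 93.6% | 0.4 |
| | 10-50% | 90.0% | 91.6% | 1.6 |
| | 5-60% | 85.3% | 89.3% | 4.0 |
| +10 points, 44 per arm per disease, evenly spaced rates | 20-40% | 67.8% | 68.4% | 0.6 |
| | 10-45% | 69.5% | 71.9% | 2.4 |
| | 5-55% | 69.0% | 73.7% | 4.7 |

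The loss depends on the effect size. At odds ratio 1.7 with 37 per arm per disease, it is 0.5 (74.8% against 75.3%), 3.0 (69.0% against 72.0%) and 6.7 points (60.9% against 67.5%) for the spreads 20-40%, 10-50% and 5-60%.

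**4. If disease is not a stratum.** Under simple randomisation the χ² held its level at about 5% in every scenario, with a ratio of nominal to true SE of about 1.00. What remains is lost power.

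**5. Continuous outcomes.** Let σ² be the common variance and r the correlation between baseline and final value. Per-patient variances are σ² for the final value, 2σ²(1 − r) for change, and σ²(1 − r²) for ANCOVA. The ANCOVA reduction is therefore r² against final values and 1 − (1 + r)/2 = (1 − r)/2 against change.

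| r (assumed) | Against final values | Against change scores |
|---|---|---|
| 0.5 | 25% | 25% |
| 0.7 | 49% | 15% |

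The article does not say which of the two the t tests would compare. This part does not depend on the strata. Disease is also a natural covariate here on the article's own terms: the diagnostic criteria require prolactin of at least 30 ng/ml for hyperprolactinemia and FSH above 25 for premature ovarian insufficiency, and both hormones are secondary outcomes.

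**The case against.** - **The strata are unnamed.** This is correct, and it matters. Six hospitals recruiting 88 women each make centre as plausible a factor as disease. A conservative level with respect to disease therefore cannot be asserted as fact.
- **Different prognosis is not documented.** Also correct. The sample size section speaks of sensitivity to treatment by disease, not of background pregnancy rates, so every power figure for pregnancy is conditional on an assumed spread.
- **The simulated trial is stylised.** Equal numbers per disease are assumed; the article's 88 is per hospital. Diseases may be suspended at the interim and the sample size recalculated, so the final set may be smaller and uneven.
- **Sparse cells.** Crossing six diseases with six centres gives up to 36 cells of about 528/36 ≈ 15 women. A fully crossed CMH test may not suit, and the fix has to allow for that.
- **Adjustment belongs in the analysis plan.** This would stand if the article were silent. It names specific tests for each variable type, none stratified or adjusted, so the point concerns what is stated.

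A reader might infer that ignoring the strata gives misleading error bars and so a risk of a false claim of benefit. The documents do not support that. In the scenarios examined the standard error is right or too wide, never too narrow, and the type I error is about 5% or lower. The article also announces no confidence intervals, only tests and descriptive summaries.

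**Conclusion.** The point holds as a matter of efficiency. The tests named are valid but use neither the randomisation strata, nor disease, nor the recorded baseline values. For pregnancy, at an odds ratio of 2.0 or a gain of 10 points, the cost is nil with equal rates, about half a point for a mild spread, 1.5 to 2.5 points for a moderate one and 4 to 5 points for a wide one. A conservative level is added only if disease is a stratum. For continuous outcomes the gain may be larger: 25% to 49% of the variance against final values, or 25% down to 15% against change scores, for r from 0.5 to 0.7. These sizes rest on assumed rates and correlations and on equal enrolment by disease. The mismatch between the stated design and the stated tests does not. It is worth correcting because the correction is nearly free, not because the trial's error rate is in danger.

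**What to change.** - **State the strata** actually used in the randomisation.
- **Primary outcome.** Use a Cochran-Mantel-Haenszel test with a common risk difference, stratified by disease and by the randomisation strata. Fix in advance what happens if cells are sparse: pool strata by a stated rule, or use logistic regression with treatment, disease and centre as main effects. Say how diseases suspended at the interim enter the analysis.
- **Second objective.** Add a treatment-by-disease interaction test, reported with the effect in each disease.
- **Continuous outcomes.** Use ANCOVA on the baseline value, disease and centre, with log transformation where skewed, in place of the unadjusted t test, ANOVA or Mann-Whitney.

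The cost is wording in the analysis plan. The data are already collected, and no further patients are needed. The change must be made before unblinding; because the interim analysis involves a first unblinding, that means before the interim if it has not yet taken place.

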### End-of-treatment visit

The information to be collected and the procedure will be the same as in the baseline visit, including general vital signs, safety index, and effectiveness index. If the participant is pregnant, the transvaginal ultrasound will be skipped. The clinical investigator will inform every unpregnant participant that she will be contacted by phone every 3 months to have a follow-up visit until she is pregnant or until 12 months after the end of treatment. If the participant is pregnant in the treatment or follow-up stage, phone follow-up will be continued until there is a pregnancy outcome.

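### Last-observation-carried-forward counts every woman who drops out before conceiving as not pregnant, and sets change to zero for outcomes measured only at baseline and end of treatment

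*Protocol article*

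**What the plan says.** The Statistical analysis section of the protocol article states that, if there are dropouts, "the last-observation-carried-forward principle will be used to compensate for the loss of data". The rule is not limited to any type of outcome. Withdrawal criteria adds: "Case record forms for withdrawn participant will be kept, and the results of the last trial will be considered final".

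The same section counts as a dropout a woman who has not explicitly withdrawn but no longer takes part in study procedures. The reasons it gives for withdrawal are "perceiving lack of efficacy; intolerance of certain adverse effects; inability to continue the clinical study; and lost to follow-up without explanation".

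On the primary outcome, the protocol says: "The primary outcome is pregnancy rate (confirmed by serum β-HCG positivity)". Under Interventions and Treatment visit, pregnancy ends treatment. End-of-treatment visit sets up later contact. This is what each woman who is not pregnant is told there: "she will be contacted by phone every 3 months to have a follow-up visit until she is pregnant or until 12 months after the end". The 12 months run from when treatment ends.

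Table 1 schedules AMH and inhibin B, the detailed transvaginal ultrasound (volumes, endometrium, antral follicle count, blood flow) and coagulation at the baseline and end-of-treatment visits only. The expected dropout rate under Sample size estimation is 20%.

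**The concern.** Pregnancy is a yes/no event that ends treatment when it occurs. The last observation of a woman who drops out before conceiving can therefore only be not pregnant, and carrying it forward declares her a treatment failure without finding out. Many of the listed reasons, such as perceived lack of efficacy or intolerance of side effects, do not imply that her outcome is unobtainable. Yet the three-monthly follow-up is arranged at the end-of-treatment visit, and no section says that women who leave early stay in it. The plan thus imputes some outcomes that it could have collected.

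For outcomes with one baseline and one end value, the last observation of a dropout is her baseline value. Her change is recorded as exactly zero and then analysed as if it had been measured.

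Three things are at stake: dilution of the treatment effect when dropout is equal between arms, bias in either direction when it is not, and standard errors that treat filled-in values as data.

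**Working it through.** **Inputs from the protocol.** Total sample size 528, allocation 1:1, so 528/2 = 264 per arm. Expected dropout 20%, so 0.20 × 528 ≈ 106 women, or about 53 per arm, would have carried-forward values. About 0.80 × 264 ≈ 211 per arm would be observed.

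**The plan's own figure.** The stated 219 per group (90% versus 80% total effective rate, β = 0.10) is reproduced by a one-sided 0.05 formula with pooled variance in both terms, which gives 218.4, rounded up to 219. The total is close to 219 × 1.2 × 2 = 525.6, against the stated 528. This point rests on neither result; only the 20% dropout and the 264 per arm are used below.

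**Inputs that are assumptions.** The protocol gives no pregnancy rates and no dropout by arm. The illustrations assume pregnancy rates of 40% versus 30% (and 30% versus 20%). They also assume that all dropouts leave before conceiving and would have conceived at their arm's rate, and that the test is two-sided at 0.05.

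**Pregnancy, equal dropout.** Rate under carry-forward = (1 − d) × true rate.
- 0.8 × 0.40 = 0.32 and 0.8 × 0.30 = 0.24. The difference falls from 10 to 8 points.
- 0.8 × 0.30 = 0.24 and 0.8 × 0.20 = 0.16. Again 10 becomes 8 points.

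Power = Φ[(difference − 1.96 × SE₀)/SE₁], where SE₀ uses the pooled rate and SE₁ the two separate rates. For 32% versus 24% with 264 per arm, SE₀ = 0.0391 and SE₁ = 0.0389, so power = Φ[(0.08 − 1.96 × 0.0391)/0.0389] ≈ 0.53.

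| Assumed rates | Every outcome obtained (264/arm) | Observed 80% only (211/arm) | Carry-forward (264/arm) |
|---|---|---|---|
| 40% vs 30% | 67.4% | 57.7% | 53.5% |
| 30% vs 20% | 75.7% | 66.1% | 63.3% |

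**Pregnancy, unequal dropout (assumed splits, experimental/control).**
- No true effect, 30% in both arms, dropout 25%/15%: 0.75 × 0.30 = 22.5% versus 0.85 × 0.30 = 25.5%. This is a spurious 3 points, with about a 12% chance of rejection in that direction against a nominal 2.5%.
- True 40% versus 30%, dropout 15%/25%: 0.85 × 0.40 = 34% versus 0.75 × 0.30 = 22.5%. The difference is inflated to 11.5 points.
- The same true rates, dropout 25%/15%: 0.75 × 0.40 = 30% versus 0.85 × 0.30 = 25.5%. The difference shrinks to 4.5 points.

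**Outcomes measured only at baseline and end.** If completers change by Δ on average and a fraction d are given zero, the analysed mean change is (1 − d) × Δ + d × 0 = (1 − d) × Δ. At d = 0.20 this is 0.8Δ, a shrinkage of 20%. It does not apply to basal body temperature, ovulation, sex hormones or the symptom score, which are also recorded during treatment.

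**The case against.** **The comparator matters.** The fall from 67% to 53% needs every dropout's outcome to be recovered, which cannot happen if some women withdraw consent or disappear. Against an analysis of the observed 211 per arm, carry-forward costs about 3 to 4 points of power, not 12 to 14. This objection stands, and it is why both comparators are shown. The assumption that all dropouts leave before conceiving and would have conceived at the full arm rate is also at the unfavourable end.

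**Missing as not pregnant is a familiar convention.** With equal dropout it dilutes the effect and does not favour the new treatment. That is true, and it remains useful as a sensitivity analysis. With unequal dropout it is not reliably conservative, as the 11.5-point case shows. Double-dummy blinding makes unequal dropout less likely but does not exclude it, and the protocol does not list adverse events by arm.

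**Reachability is an inference.** The protocol does not say that women who drop out can be contacted, and those lost without explanation may not be. A phone call would also not settle the outcome by itself, because pregnancy is confirmed by serum β-HCG. The Primary outcome section gives no time window either, so counting pregnancies from the follow-up stage is itself an assumption.

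**Two stronger readings are not supported.**
- A reader might infer from "If the participant is pregnant, the transvaginal ultrasound will be skipped" that carry-forward would give women who conceive their baseline ultrasound as an end value. The rule covers dropouts only. Women who conceive go on to the end-of-treatment visit and follow-up, so the text does not make them dropouts.
- A reader might also infer that a woman with a serious adverse event, of whom the Safety analysis section says "she will be removed from the trial as soon as possible and provided proper treatment", has her last result fixed as final. That rule is written for withdrawn participants, and Safety analysis says nothing about how the data of removed women are handled.

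**Conclusion.** The concern holds in this form. Carry-forward for all dropouts is a stated rule, not a detail left open, and an analysis plan that followed it would inherit the problem.

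The firmest part is the set of outcomes scheduled only at baseline and end of treatment. There the rule makes a dropout's change zero by construction, which shrinks a mean change by about 20% at the planned dropout, and single imputation misstates the standard errors.

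For pregnancy, the rule forces a failure on any woman who drops out before conceiving. The documents do not fix the size of the effect, because the pregnancy rates and the dropout by arm are assumptions. Under those used here, a 10-point difference becomes 8 points with equal dropout. The power loss is about 3 to 4 points if the dropouts' outcomes are truly unobtainable, and up to 12 to 14 points if all of them could have been obtained. Unequal dropout could inflate, shrink or create a difference. The rule should be replaced.

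**What to change.** 1. In the protocol, separate stopping treatment from withdrawing from the study. The clinical decision to stop is untouched.
2. Continue the existing pregnancy follow-up, with the same confirmation of pregnancy, for every randomised woman who has not withdrawn consent, and analyse all women as randomised.
3. For pregnancy outcomes still missing, use multiple imputation, with missing counted as not pregnant as a sensitivity analysis.
4. For continuous outcomes measured repeatedly, use a mixed model for repeated measures. For those with one post-baseline value, use baseline-adjusted ANCOVA on observed or multiply imputed data.
5. Remove the carry-forward sentence from Statistical analysis and bring the sentence on last results in Withdrawal criteria into line.

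The cost is a wording change with the ethics amendment that the protocol requires for modifications, some extra contacts and visits for women who stop early, and slightly more analysis work. The follow-up part is urgent, because outcomes that were not collected cannot be recovered by a later analysis.
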